#### Propensity Score

For residual confounding after randomization, we will use propensity scores based on inverse probability of treatment weighting [55]. We will first assess the covariate balance between control and intervention groups through standardized mean differences and differences in proportion. Covariates will include the patient demographic and clinical variables. Values greater than 0.1 will signal an imbalance in covariates. Next, we will use inverse probability of treatment weighting generated through logistic regression to balance the covariates [56]. Once we achieve covariate balance, we will estimate the effect for each outcome by using a double robust approach.

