#### Patient Demographic and Clinical Variables

Age, gender, education, marital status, cancer diagnosis and staging, oncological treatments, BMI, alcohol and smoking habits, and comorbid medical disorders are collected through electronic medical records.

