### Timeline

There are 3 assessment time points. At the baseline (T0), all patients fill a set of validated measures (MMAS-8, AAI, STAI-Y forms I and II, BDI-II, CBI-B/I, SOC-13, BPI, EORTC-QLQ-C30, EORTC-QLQ-BR23, BFI, and visual analogue scale). The expected time to complete all the given questionnaires at baseline is approximately 40 minutes. Access to DSS is given to the experimental group for 3 months. At T1 and T2, the following questionnaires are filled: MMAS-8, AAI, STAI-Y form I, BDI-II, CBI-B/I, EORTC-QLQ-C30, and EORTC-QLQ-BR23. Further, all patients have to fill a weekly adherence medication diary for 3 months. Variables that are not sensitive to change, for example, personality (BFI) and anxiety traits (STAI-Y form II) are collected only at T0. Each month, all participants receive a brief telephone interview in which they are monitored for adherence to the research protocol. Two psychologists perform the monthly telephone interview to monitor the filling out of the questionnaires and the medication adherence diary supporting patients with MBC in this task, barriers, and concerns related to the study participation. At T3 (3 months), all behavioral and psychological measures are filled, and an interview (online or vis-à-vis) is performed.

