#### Generalized Linear Models

Additional analyses will be run using generalized linear models with a Gaussian distribution family (multiple linear regression) being adjusted for randomization baseline imbalances. These models will evaluate the association between all previously reported outcomes (the number of pills taken during the prescribed interval, MMAS-8, AAI, STAI-Y, BDI-II, CBI-B/I, SOC-13, BPI, EORTC-QLQ-C30, EORTC-QLQ-BR23, BFI, and risk perception) and the intervention (TREAT and machine learning web application), accounting for the baseline differences. We will build one model for each combination of predictor and outcome, where the outcome will be the dependent variable (Y) and the predictor will be the independent variable (X), adjusted for the covariates unbalanced at baseline. We will also evaluate models with a Poisson or negative binomial distribution for non–normally distributed outcomes. Results will be reported as predicted means along with 95% CIs.

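### Adjustment covariates are chosen by an observed imbalance above 0.1, which chance alone produces for about 62% of covariates on the standardised scale at 50 per arm; the baseline MMAS-8 and AAI scores are not among the named covariates

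*Protocol article*

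**What the plan says.** The Propensity Score section of the protocol article aims to deal with confounding thought to remain after randomisation. It will "assess the covariate balance between control and intervention groups through standardized mean differences and differences in proportion" and adds that "Values greater than 0.1 will signal an imbalance in covariates". On which variables are meant, it says "Covariates will include the patient demographic and clinical variables". The section of that name under Measures lists them: "Age, gender, education, marital status, cancer diagnosis and staging, oncological treatments, BMI, alcohol and smoking habits, and comorbid medical disorders are collected" from the medical records. No adherence score is in that list. Inverse probability of treatment weighting follows, and then a doubly robust estimate for each outcome.

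The Generalized Linear Models section builds one model per predictor and outcome, "adjusted for the covariates unbalanced at baseline". It also says the models relate the outcomes to the intervention "accounting for the baseline differences". The outcomes include the pill count, MMAS-8 and AAI, which are the three adherence measures named in the Primary End Point Analysis section.

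The Timeline section shows that the baseline scores exist: "At the baseline (T0), all patients fill a set of validated measures (MMAS-8, AAI", followed by the other questionnaires.

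**The concern.** Under valid 1:1 randomisation, baseline differences between arms are chance, and the standard error of the treatment effect already allows for them. A covariate is worth adjusting for because it predicts the outcome, not because it happens to differ between arms. A rule based on observed imbalance can bring in a covariate that predicts nothing and leave out a strong predictor that happens to be balanced.

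Two things are at stake. First, the model cannot be written down until the data have been seen, and at this sample size the threshold is so low that chance decides most of its content. Second, for a 3-month MMAS-8 or AAI score the natural covariate is the same score at T0. It is collected but not named, so precision that costs nothing further may go unused.

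**Working it through.** **Inputs from the protocol article.** Allocation is 1:1 without stratification (Randomization). There are 50 patients per arm, expanded to 120 in total for attrition; the difference is 0.51, the SD 1.2, α .05 two-sided, and the stated power 96.4% (Calculation of Sample Size). The threshold is 0.1 (Propensity Score).

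**The plan's own figure.** The article gives no chance rate for the 0.1 threshold. The only related design figure is the power:
- SE of the difference = 1.2 × √(2/50) = 0.24
- 0.51 / 0.24 = 2.125
- Power ≈ Φ(2.125 − 1.96) = Φ(0.165) ≈ 56.6% (55.7% by the noncentral t)

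The stated 96.4% is not reproduced. That is a separate matter, and the chance-imbalance result does not depend on it. The recomputed 57% is the starting point for the power comparison below.

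**Chance imbalance on the standardised scale.** Under randomisation a standardised difference is approximately N(0, 2/n), with n per arm.
- SE = √(2/50) = 0.20
- P(|SMD| > 0.1) = 2 × [1 − Φ(0.1/0.20)] = 2 × [1 − Φ(0.5)] = 61.7%
- Checks at 50 per arm: t distribution 61.8%; simulation of 100,000 trials 61.5%; exact enumeration for binary covariates with prevalence 0.1 to 0.5, 59% to 64%
- At 60 per arm 58.4%; at 40 per arm 65.5%
- For chance to exceed 0.1 in only 5% of covariates: n = 2 × (1.96/0.1)² ≈ 768 per arm

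Ten independent covariates, all on this scale, would give 10 × 0.617 ≈ 6 flagged by chance.

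**Chance imbalance if raw differences in proportion are meant.** Exact probabilities of a difference strictly above 0.1 at 50 per arm:

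| Prevalence | P(raw difference > 0.1) |
|---|---|
| 0.1 | 6.6% |
| 0.2 | 16.8% |
| 0.3 | 23.0% |
| 0.5 | 27.1% |

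**Value of the T0 score.** Adjusting for a baseline score with correlation r to the 3-month score reduces the residual SD to 1.2 × √(1 − r²). The article gives no r, so a range is assumed:

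| r (assumed) | Residual SD | SE | Power |
|---|---|---|---|
| none | 1.200 | 0.240 | 56.6% |
| 0.3 | 1.145 | 0.229 | 60.6% |
| 0.5 | 1.039 | 0.208 | 68.9% |
| 0.7 | 0.857 | 0.171 | 84.5% |

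**The case against.** **The scale.** Many listed covariates are categorical, and gender cannot vary because only women are eligible. The text names both standardised mean differences and differences in proportion without saying whether the latter are standardised. This stands: 62% cannot be quoted for every covariate, and the raw reading gives 7% to 27%. Even so, a binary covariate of moderate prevalence would then be flagged by chance in up to about a quarter of trials.

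**Whether T0 scores are excluded.** A reader might infer that the plan deliberately leaves them out. The text does not go that far. The verb used for the covariates is not exhaustive, the phrase "accounting for the baseline differences" could be meant to cover T0 scores, and an article may leave the full list to the full protocol or analysis plan. What can be said is that the scores are not named. The selection rule itself is stated, so it is not a detail left to another document.

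**What the trigger governs.** A reader might infer that weighting is switched on by the 0.1 rule, or repeated until balance is reached. Neither is described: balance is assessed, then weighting is applied. The data-driven choice is explicit only in the Generalized Linear Models section, which calls its analyses additional, while the sample size assumes a two-sample t test. So the documents do not support saying that the primary estimate as such is unspecified.

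**Type I error.** A reader might also infer that doubly robust weighting inflates the false positive rate. That depends on a variance estimator the article does not state. In one simulation with 10 covariates at 50 per arm (1,500 trials, assumed covariate R² of 0.3), a true null was rejected in 7.8% of trials with model-based standard errors and in 4.8% with HC3 robust ones. No claim of inflation is made.

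**Reach of the precision gain.** The diary pill ratio has no T0 value. Patients may be switching to a new oral treatment at enrolment, so T0 MMAS-8 may refer to a different drug and correlate less with the 3-month score. Both points stand, and they are why the gain is confined to MMAS-8 and AAI and shown from r = 0.3 upwards.

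**Conclusion.** The point holds in this form. The article fixes a rule that selects outcome-model covariates by observed imbalance, and in a randomised trial of this size chance largely decides what the rule picks: about 62% of covariates at 50 per arm on the standardised scale, 58% at 60 per arm, and about 7% to 27% of binary covariates if raw differences in proportion are intended. The link between the two sections rests on the 0.1 threshold being the only definition of imbalance in the article.

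The T0 MMAS-8 and AAI scores are collected but not named as covariates. Adjusting for them would raise power by roughly 4 to 28 percentage points over assumed correlations of 0.3 to 0.7. Those figures use the article's difference and SD, which come from satisfaction with the treatment decision and not from an adherence scale, so they show the possible gain and do not forecast it. This should be corrected before the data are analysed; it does not by itself invalidate the trial's comparison.

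**What to change.** In the Propensity Score and Generalized Linear Models sections, and in the analysis plan:

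- Remove the 0.1 threshold as the rule for choosing covariates. If balance is still tabulated, treat it as descriptive and say whether differences in proportion are raw or standardised.
- Pre-specify a short list of covariates chosen for expected prognostic value, and use it in every outcome model whatever the observed imbalance.
- In the 3-month MMAS-8 and AAI models, include the T0 value of the same score (analysis of covariance). For the pill ratio, use the pre-specified list and state that it has no baseline value of its own.
- Keep inverse probability weighting as a sensitivity analysis.

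The cost is analysis wording only, because the T0 scores are already collected from all patients. If an analysis plan already fixes the covariates, bring the two documents into line.

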#### Generalized Linear Models

Additional analyses will be run using generalized linear models with a Gaussian distribution family (multiple linear regression) being adjusted for randomization baseline imbalances. These models will evaluate the association between all previously reported outcomes (the number of pills taken during the prescribed interval, MMAS-8, AAI, STAI-Y, BDI-II, CBI-B/I, SOC-13, BPI, EORTC-QLQ-C30, EORTC-QLQ-BR23, BFI, and risk perception) and the intervention (TREAT and machine learning web application), accounting for the baseline differences. We will build one model for each combination of predictor and outcome, where the outcome will be the dependent variable (Y) and the predictor will be the independent variable (X), adjusted for the covariates unbalanced at baseline. We will also evaluate models with a Poisson or negative binomial distribution for non–normally distributed outcomes. Results will be reported as predicted means along with 95% CIs.

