**Objective:**

The primary end point is to evaluate the effectiveness of a decision support system (DSS) and a machine learning web application in promoting adherence to oral anticancer treatments among patients with metastatic breast cancer. The secondary end point is to collect a set of new physical, psychological, social, behavioral, and quality of life predictive variables that could be used to refine the preliminary version of the machine learning model to predict patients’ adherence behavior.

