### Secondary End Point Analysis

The secondary end points were to identify clinical (comorbidities, presence of pain, tumor type, type of treatment), psychological (personality traits, anxiety, depression, self-efficacy for coping with cancer, sense of coherence, and risk perception), and QoL variables predicting patients’ adherence to OATs. These variables are used as predictors for evaluating nonadherence to OATs among patients with MBC and for enriching the preliminary version of a machine learning model developed in the retrospective study. Our initial machine learning models that are evaluated as an intervention in this study were built based on variables extracted from clinical notes by using natural language processing. Once the data collection for this study is complete, we will also use the data collected to improve our initial machine learning models. Data for the secondary end points are collected using the European Organization for Research and Treatment of Cancer QoL Questionnaire Core 30 (EORTC-QLQ-C30) [33,34], European Organization for Research and Treatment of Cancer QoL 23-item Breast Cancer-specific Questionnaire (EORTC-QLQ-BR23) [35], and the Brief Pain Inventory (BPI) [36]. To evaluate psychological variables, we used the State-Trait Anxiety Inventory (STAI-Y) [37,38], Beck Depression Inventory-II (BDI-II) [39,40], Big Five Inventory (BFI) [41], Brief Italian version of Cancer Behavior Inventory (CBI-B/I) [42,43], 13-item Sense of Coherence scale (SOC-13) [44], and risk perception (using 2 visual analogue scales) [45,46].

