## Discussion

### Expected Findings

Adherence to anticancer treatment is fundamental in the clinical management of patients with MBC, as adherence can lead to a series of crucial clinical outcomes (eg, prolonged survival time, better monitoring and management of side effects, improvement of QoL) [1-6]. Studies on implementing machine learning to foster medication adherence as well as the development of shared DSSs are quite recent [23].

We believe that our study might achieve 3 milestones in the clinical care of patients with MBC with regard to adherence to OATs. Concerning the primary end point, implementing a shared and integrated DSS web-based solution might be an essential strategy for patients with MBC to enhance their health knowledge and understanding of medication nonadherence issues and to learn behavioral strategies to overcome individual, disease-related, and organizational barriers impacting adherence behaviors. This expected result is coherent with the results of other studies on patient decision tools, highlighting that such engines might improve patients’ participation and health knowledge in the care pathway [61]. Regarding the secondary end point, this prospective study will contribute to refining the initial risk-predictive model of adherence attained from the retrospective study, informing about specific (inner and external) predictors of adherence behavior during the MBC care pathway that were not considered in the preliminary version of the model. This should provide a more comprehensive and systematic definition of medication adherence for OATs in patients with MBC, defining an interrelated and evidence-based list of predictors. Data will define a final risk-predictive model of adherence and enable the identification of specific patient populations at risk of nonadherence. The earlier identification of patients with poor adherence using our machine learning web application will permit the development of tailored psychological and behavioral interventions to foster adherence by dealing with individual barriers and needs according to the risk profile. Finally, the information retrieved by the risk-predictive models might support oncologists’ treatment decisions, allowing them to better understand the hindered reasons behind a complex adherence trajectory.

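### The written-out regressions make the secondary end point's predictors into outcomes of the intervention, and the promised final risk model is not supported by about 100 patients

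*Protocol article*

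**What the plan says.** The abstract's Objective gives the secondary aim as to "collect a set of new physical, psychological, social, behavioral, and quality of life predictive variables" for refining the machine learning model. Secondary End Point Analysis says the same of the clinical, psychological and quality-of-life variables: "These variables are used as predictors for evaluating nonadherence to OATs among patients with MBC and for enriching the preliminary version" of the machine learning model. It adds that the trial data will be used afterwards to improve the initial models.

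Generalized Linear Models is the only place where regressions are written out. It says "These models will evaluate the association between all previously reported outcomes" and the intervention. After the three adherence measures, the list runs: "STAI-Y, BDI-II, CBI-B/I, SOC-13, BPI, EORTC-QLQ-C30, EORTC-QLQ-BR23, BFI, and risk perception) and the intervention (TREAT and machine learning web application"). One model is built per predictor and outcome pair, in which "the outcome will be the dependent variable (Y) and the predictor will be the independent variable (X"), adjusted for covariates found unbalanced at baseline.

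Timeline collects every listed scale at T0. For the middle visits, "At T1 and T2, the following questionnaires are filled: MMAS-8, AAI, STAI-Y form I, BDI-II, CBI-B/I, EORTC-QLQ-C30, and EORTC-QLQ-BR23". BFI and trait anxiety (STAI-Y form II) are taken at T0 only, because they are regarded as insensitive to change.

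Expected Findings states: "Data will define a final risk-predictive model of adherence and enable the identification of specific patient populations at risk of nonadherence".

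**The concern.** The secondary end point runs from the scales to adherence. The written-out models run from the intervention to the scales. An analyst who follows Generalized Linear Models would produce a table of intervention effects on anxiety, depression, quality of life and so on. Those regressions would not show which of these variables predicts adherence. At least one model, that for BFI, would compare a baseline trait between randomized arms, which is a balance check and not an effect.

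Expected Findings nevertheless promises a final predictive model and identified at-risk populations. If readers take that at face value, a model resting on few patients under mixed exposure could be used to select patients for tailored intervention.

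**Working it through.** **1. Direction of the models.**

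| | Secondary End Point Analysis | Generalized Linear Models |
|---|---|---|
| Psychological and quality-of-life scales, pain, risk perception | predictors (X) | outcomes (Y) |
| Adherence | what is predicted (Y) | one of the outcomes (Y) |
| Intervention | not mentioned in the prediction | the only named predictor (X) |

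Adherence does appear as Y, but against the intervention. Demographic and clinical variables may enter those models as adjustment, chosen because they are unbalanced and not because they predict. No written-out model has adherence as Y and the scales as X.

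**2. Baseline-only traits.** An intervention effect needs a value measured after the intervention starts. BFI has none. STAI-Y is listed without naming the form: form I is repeated, form II is not. Timeline also says that all behavioral and psychological measures are filled at T3, but its explicit restriction of BFI and form II to T0 is the more specific statement.

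**3. Where the link from new predictors to adherence can come from.**
- The Pfizer Project section says the added predictors are not available in the retrospective data (2750 patients).
- Limitations of This Trial says the initial application could not directly predict adherence.
- That leaves the trial: 100 patients, 50 per group (120 with the attrition allowance).
- Under Randomization, one group gets the decision support system with training, and the other gets standard care with suggestions that bolster adherence.

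**4. Size.** The plan gives no figure for the prediction aim. Calculation of Sample Size concerns a two-group t test only, and nothing below uses it.

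Candidate predictors, my count from Measures:
- 11 with one score per instrument (two each for STAI-Y and risk perception);
- 32 with the listed subscales (BR23 counted as one);
- 41 with nine demographic and clinical variables added.

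A finer split could reach about 55.

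Patients per predictor: 100/11 = 9.1, 100/32 = 3.1, 100/41 = 2.4.

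Expected apparent R-squared with no true association, unpenalised linear regression, n = 100, is p/(n − 1):
- 11/99 = 0.11
- 32/99 = 0.32
- 41/99 = 0.41
- 55/99 = 0.56

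Minimum n for an expected shrinkage factor S = 0.9 is n = p / [(S − 1) ln(1 − R²/S)]. The true R² is an assumption:

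| p | R² = 0.2 | R² = 0.3 | R² = 0.5 |
|---|---|---|---|
| 11 | 438 | 272 | 136 |
| 32 | 1274 | 790 | 395 |
| 41 | 1632 | 1012 | 506 |

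Every entry exceeds 100.

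**The case against.** **A scale may have both roles.** It can be a baseline predictor of adherence and also an outcome of the intervention, and Generalized Linear Models describes itself as additional analysis. This stands: listing the scales as outcomes is not wrong in itself. What remains is that the other direction is never written as a regression, and that baseline-only traits cannot be outcomes.

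**The phrase about each combination of predictor and outcome may cover the secondary aim.** No predictor other than the intervention is named. Even a generous reading gives one-variable-at-a-time models with no stated arm term.

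**The machine learning refinement answers the secondary end point.** A reader might infer that the trial would report nothing on what predicts nonadherence. The document does not support that, because Secondary End Point Analysis keeps this route open. Its algorithm, time points and validation may be set out in the full protocol or analysis plan, and their absence from the article is not the complaint.

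**Arm contamination.** A reader might infer that an intervention shifting both a scale and adherence would create many spurious predictors. That needs post-baseline values pooled without an arm term, which the document nowhere plans. With T0 values it cannot arise, since randomized allocation is independent of them. At the document's only effect size, 0.42 on both variables and no within-arm correlation, the pooled correlation is about 0.42²/4 ÷ (1 + 0.42²/4) = 0.0441/1.0441 = 0.04. The false-positive rate is then about 7% instead of 5%. Much larger rates need shifts of 0.6 SD or more in both, which nothing in the document supports.

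**The overfitting figures assume a joint unpenalised model.** The plan does not propose one. Penalised methods would reduce the optimism, but would not make a model from about 100 patients final.

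**Expected Findings is Discussion text with hedged opening words.** True, but the sentence on the final model is unhedged.

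**Conclusion.** The point holds in a limited form. The written-out regressions do not answer the secondary end point, and they list at least one baseline-only trait as an outcome of the intervention. Both follow from the text without assumptions, apart from taking Timeline's T0-only statement at its word. The claim of a final risk model is unsupported, because the new predictors can be linked to adherence only in about 100 patients under mixed exposure.

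The apparent R-squared of 0.41 to 0.56 illustrates the scale of possible optimism. It rests on my predictor count and on unpenalised joint regression, and is not a forecast for this trial. Arm contamination is a conditional and small risk and does not carry the point. The primary comparison is not affected.

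**What to change.** - **Generalized Linear Models:** add a secondary analysis with 3-month adherence as Y, T0 values of the clinical, psychological and quality-of-life variables as X, and randomized arm as a covariate.
- **Secondary End Point Analysis:** state that the model refinement uses T0 values and arm, and that performance will be cross-validated or bootstrap-corrected.
- **Outcome list:** keep intervention effects on the repeatedly measured scales as a separate analysis. Remove BFI and trait anxiety (STAI-Y form II), and name form I where STAI-Y stays.
- **Expected Findings:** describe the result as exploratory candidate predictors that need validation in other patients, in place of a final model and identified risk populations.

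The cost is wording and some analysis time. All listed scales are already collected at T0 and the clinical variables come from the medical record, so no new data are needed. The downside is a more modest secondary claim.

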## Methods

### Primary End Point Analysis

The primary end point was to assess the effectiveness of the DSS web-based solution and the machine learning web application in promoting adherence to OATs in a sample of 100 patients with MBC at 3 months. The adherence is evaluated using the number of pills taken divided by the number of pills prescribed. Further, the adherence is assessed using behavioral measures: the 8-item Morisky Medication Adherence Scale (MMAS-8) [31] and Adherence Attitude Inventory (AAI) [32].

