#### Inclusion and Exclusion Criteria

The inclusion criteria were female patients with MBC, 18 years of age and older, with a prescription of oral treatment (eg, oral chemotherapy, endocrine therapy, cyclin-dependent kinase 4/6 inhibitors), having internet access and a personal smartphone or tablet, and ability to read and sign informed consent. The exclusion criteria were the presence of any primary psychiatric or neurological conditions.

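### The regression section names the raw number of pills taken as the adherence outcome, whereas the primary end point is pills taken divided by pills prescribed, and no denominator or offset is stated

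*Protocol article*

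**What the plan says.** Under Primary End Point Analysis the protocol article states: "The adherence is evaluated using the number of pills taken divided by the number of pills prescribed". The Adherence Medication Diary section says that the weekly diary records pills not taken, pills prescribed and planned interruptions, so both parts of the ratio will be available.

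The Generalized Linear Models section announces "generalized linear models with a Gaussian distribution family (multiple linear regression) being adjusted for randomization baseline imbalances". It then says: "These models will evaluate the association between all previously reported outcomes". In the list that follows, the pill outcome is "the number of pills taken during the prescribed interval". For outcomes that are not normally distributed it adds: "We will also evaluate models with a Poisson or negative binomial distribution". The stated adjustment is that models are "adjusted for the covariates unbalanced at baseline". Pills prescribed appears neither as a denominator, nor as an offset, nor as a named covariate.

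The inclusion criteria admit several drug classes: "oral treatment (eg, oral chemotherapy, endocrine therapy, cyclin-dependent kinase 4/6 inhibitors". Randomization is 1:1 without stratification.

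**The concern.** The two sections describe different quantities. A patient who takes 63 of 63 pills (100%) and one who takes 63 of 84 (75%) have the same value of the regression outcome but quite different adherence.

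If the regression section is followed as written, differences in prescribed pill load enter the outcome as noise. Three things are at stake:
- The treatment effect is reported in pills rather than as adherence.
- Power is lower than the ratio would give.
- If the Poisson option is used with its model-based standard errors, the type I error rate exceeds 5%, because variation between and within regimens is far larger than Poisson variation.

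The mention of count families makes the literal reading more likely, since pills taken is the only count in the list. If the phrase was meant as the ratio, Poisson and negative binomial are poor choices for a bounded proportion. The passage needs correction on either reading.

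**Working it through.** **The plan's own figure.** No figure in the article rests on the pill outcome. The sample size section uses a difference of 0.51 and SD 1.2 on a satisfaction scale. With 50 per arm those inputs give z = (0.51/1.2) × √25 = 2.125 and power Φ(2.125 − 1.96) = 56.5%, not the stated 96.4%. That is a separate matter and is not used below.

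**Inputs.** From the article: 50 per arm, two-sided α 0.05. Assumed, because the article gives no values: adherence A with mean 0.86 (control) and 0.92 (intervention), SD 0.12; prescribed 3-month totals R, independent of A, in four mixes:
- wide: 84/147/392 pills in 25/50/25% of patients
- milder: 63/84/168 in 40/40/20%
- narrow: 63/84 in 50/50%
- a single regimen of 84 pills

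**Ratio.** z = 0.06 / (0.12 × √(2/50)) = 0.06/0.024 = 2.5. Power = Φ(2.5 − 1.96) = 70.5%, whatever the mix.

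**Unadjusted count, T = R × A.** With mean adherence a, Var(T) = E[R²](a² + 0.0144) − E[R]²a². The expected difference is 0.06 × E[R], its standard error is √((Var₀ + Var₁)/50), and power is Φ(z − 1.96) + Φ(−z − 1.96).

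| Mix | E[R] | E[R²] | Difference (pills) | SE | z | Power |
|---|---|---|---|---|---|---|
| Wide | 192.5 | 50984.5 | 11.55 | 21.71 | 0.53 | 8.3% |
| Milder | 92.4 | 10054.8 | 5.54 | 7.34 | 0.76 | 11.7% |
| Narrow | 73.5 | 5512.5 | 4.41 | 2.58 | 1.71 | 40.0% |
| Single | 84 | 7056 | 5.04 | 2.02 | 2.50 | 70.5% |

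Simulations agree, with about 7–41% across the three mixed cases. With no true effect the t test on the count rejects in about 5% of trials (4–6% across runs).

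**Count with the planned adjustment.** The Propensity Score section flags imbalance above 0.1, and oncological treatments are among the clinical variables collected. Adding regimen to the Gaussian model only when it is flagged gives, by simulation:
- flag on a difference in proportions above 0.1: power about 30%, 34% and 48% (wide, milder, narrow)
- flag on a standardized difference above 0.1, which occurs in about 85% of trials: about 50% (wide) and 55% (milder)
- regimen always adjusted: about 58% and 63%

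Overall this is about 31–57% when adjustment depends on imbalance, against 68–74% for the ratio. The low end moves by several points with how a difference of exactly 0.1 is treated. These figures assume that the recorded treatment class captures pill load.

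**Plain Poisson, no true effect.** With D the ratio of actual to Poisson variance, type I error is about 2[1 − Φ(1.96/√D)].
- Unadjusted, D = Var(T)/(0.86 × E[R]): 66.7, 15.9 and 2.55 for wide, milder and narrow, giving 81%, 62% and 22%.
- Regimen always adjusted, D = 0.0144 × E[R²]/(0.86 × E[R]): 4.43, 1.82 and 1.26, giving 35%, 15% and 8%.
- Single regimen of 84 pills: D = 1.41, giving 10%.

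Simulation gave about 20–80% unadjusted and 9–34% adjusted. The second line applies equally to a Poisson model with log(pills prescribed) as offset, so an offset alone does not restore the error rate; robust variance is needed as well.

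**The case against.** **The phrase may be shorthand.** The section says that it covers the outcomes already reported, and the pill outcome reported earlier is the ratio. The diary collects the denominator, and an article may leave offset terms to the full protocol. This is plausible and lowers the certainty that a raw count is intended. It does not remove the conflict between two named outcomes, and the count families point the other way.

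**The models are additional.** The section labels them so, the sample size section assumes a two-sample t test for the final analysis, and the Propensity Score section promises a doubly robust estimate for each outcome. None of these replaces the ratio by a count. A reader might infer that the whole primary analysis rests on the count; the article does not support that.

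**Regimen does not bias the comparison.** A reader might also infer that regimen size rather than adherence drives the result. Randomization balances regimen in expectation, with or without stratification, and the Gaussian test keeps its 5% level. Regimen adds variance; it does not create a treatment effect.

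**The worst figures omit stated adjustment and use assumed mixes.** Both points stand. Near-total loss of power needs a wide mix and no adjustment for regimen. The 80% Poisson figure also needs model-based standard errors, and the section names the negative binomial as an alternative. On the other side, adjustment at baseline applies only if imbalance is flagged, and it cannot follow changes of treatment or interruptions after randomization, which the article itself expects.

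**Questionnaire scores.** Whether count families suit bounded scores is a secondary modelling choice and is not part of this point.

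**Conclusion.** The inconsistency is real and should be corrected before analysis. Read literally, the regression section estimates a different and noisier quantity than the adherence ratio. The Gaussian count analysis is valid under the null but less powerful and expressed in pills. The plain Poisson option is anticonservative under every mix examined; its inflation is smaller once regimen is adjusted for.

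The size rests on assumed regimen totals, adherence of 0.86 versus 0.92 and SD 0.12. A narrow mix costs a moderate amount of power, a wide mix most of it unless regimen is adjusted for, and equal regimens almost none in the Gaussian model. With adherence of 0.85 versus 0.92 and totals of 63 or 84 pills, unadjusted power falls from about 80% to 52%. The conclusion concerns the adherence regression and not necessarily every analysis of the primary end point.

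**What to change.** In the Generalized Linear Models section, replace the pill count with the ratio defined under Primary End Point Analysis: total pills taken over total pills prescribed across the 3 months, with planned interruptions removed from the denominator. Analyse it with a linear or fractional logit model with robust standard errors, and report the difference in mean ratio with its 95% CI.

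If a count model is kept, include log(pills prescribed) as an offset and use robust variance; the offset without robust variance is not enough.

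The cost is analysis wording only. The diary already collects everything needed, and neither the sample size nor the visit schedule changes.
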